## Abstract

**Background:**

Several studies have shown that individuals with intellectual disabilities (IDs) have low levels of physical activity (PA), and intervention studies on PA suggest inconsistent evidence. The use of technology as a means of motivation for PA has yet to be extensively explored and needs to be further investigated.

**Objective:**

We aim to assess the feasibility and acceptability of procedures for an intervention arm in a future trial on mobile health (mHealth) to support PA for individuals with IDs. In addition, we aim to examine how the use of technology can influence motivation for PA among participants, their caregivers, and staff members.

**Methods:**

A mixed methods pilot study of an intervention arm will be carried out in a planned randomized controlled trial (RCT). Ten participants with ID and their caregivers or a staff member will be included. Information will always be provided by a caregiver or a staff member, or participants with ID if possible. Assessments will be carried out at baseline, follow-up after 4 weeks, and 12 weeks, and include questionnaires on PA, social support, self-efficacy, and challenging behavior. PA will be measured with 2 different activity trackers (Fitbit and Axivity) for 1 week at all assessments. Feasibility will be assessed as recruitment and adherence rate, missing data, usability of the motivational mHealth tool, and estimates of effectiveness. Acceptability of study procedures, activity measures, and motivation for participation in PA will be additionally assessed with qualitative methods at the end of the intervention.

**Results:**

Enrollment commenced in May 2021. Data collection was completed in March 2022.

**Conclusions:**

This pilot study will evaluate the feasibility and acceptability of study procedures of the intervention arm of a planned RCT to address feasibility issues, improve study procedures, and estimate effectiveness of the study measures. How the use of technology can influence motivation for PA will also be examined, which can help guide and improve future PA interventions involving the use of technology.

**Trial Registration:**

ClinicalTrials.gov NCT04929106; https://clinicaltrials.gov/ct2/show/NCT04929106

**International Registered Report Identifier (IRRID):**

DERR1-10.2196/37849

## Introduction

### Physical Activity and Intellectual Disability

Compared to the general population, individuals with intellectual disability (ID) have more sedentary lifestyles, poor health, and greater barriers for participation in physical activity (PA), and consequently lower levels of PA [1-6]. PA is beneficial for cardiovascular and muscular capacity and psychological well-being and can reduce the burden of chronic disease for individuals with ID [1,7-9]. A systematic review by Hassan et al [10] investigated the efficacy of randomized controlled PA interventions, and the results showed inconsistent evidence, with only 3 intervention studies showing a prolonged effect of the intervention [8,10-12]. It is clear that new approaches and further investigations are needed to develop effective interventions for PA in this group.

Including individuals with ID in clinical intervention trials can be challenging, since there are several barriers in all aspects of the research process [13,14]. Struggling to inform the individual with ID about the research, difficulties in obtaining informed consent, finding transport to research sites, and following instructions are common challenges in clinical trials involving individuals with ID [3,15,16]. It is, therefore, particularly important to carefully plan intervention studies for this group, and performing pilot trials or feasibility studies can improve the quality of research [17].

### Use of Technology for Individuals With ID

Recent studies have shown measurable benefits from the use of mobile technologies in health care and the use of technology in everyday life has been explored and deemed promising for individuals with ID [18-21]. Although some studies have explored the possibility of using mobile technologies for promoting PA for individuals with ID, there has been only one preliminary report of a randomized controlled trial (RCT) using smartphone support to increase motivation for PA in youths and adults with ID [22-25]. In Norway, many individuals with ID have a smartphone or a tablet device they can use for tailored PA interventions and this use has not been tested. A previous study in this research project showed that individuals with ID are motivated to participate in PA and evince an interest in technology [26,27]. According to the *World Report on Disability 2011* [28], health promotion efforts targeting this population can improve lifestyle behaviors. The report states that these individuals have the right to be included in all PA programs.

### Objectives

The primary objective of this pilot study is to assess feasibility and acceptability of study procedures for a future RCT. We also aim to explore the experience of participants and their caregivers regarding the intervention, focusing on success factors, problems, and reasons for dropout, and to understand how the use of technology can influence motivation for PA for this group.

## Methods

### Study Context

This pilot study is part of a larger project, which aims to develop and test tailored mobile health (mHealth) support systems that promote PA in individuals with ID. We have previously conducted a qualitative study on motivation for participation in PA for such individuals, held workshops and collaborated with developers, and performed usability tests [26,29]. The results from this study will be used in the planning of a larger RCT with 60 participants. See [name] et al [27] for more detailed information regarding the RCT.

### Design

This protocol describes a mixed methods pilot study of an intervention arm in a planned RCT [27].

### Participant Selection and Recruitment

Eligible participants will be identified through their participation in a larger study on health indicators for individuals with ID, the Norwegian Health in Intellectual Disability (NOHID) study, and through staff leaders at municipality levels who have identified potential participants [30]. Overall, 10 participants with ID as well as caregivers and support persons (ie, staff) will be included if they have a sedentary lifestyle or low levels of PA. A sedentary lifestyle is defined as primarily engaging in reading, watching TV, or other mainly sedentary activities. A low level of PA is defined as mainly walking or other light PA for less than 4 hours a week. The number of participants is chosen on the basis of assumptions about sufficient variation for the investigation of feasibility and acceptability of the pilot study [23]. Data saturation of qualitative data collected will be evaluated continually and there will be scope for flexibility to achieve this during the data collection period.

### Inclusion and Exclusion Criteria

The inclusion criteria are as follows: (1) low levels of PA, (2) diagnosis of ID (mild, moderate, severe, or profound), (3) aged between 16 and 60 years, (4) ability to participate in the pilot study, (5) capable of walking with or without support, and (6) can provide written informed consent or consent can be obtained from a legal representative. Prior to enrollment, all participants will be screened for readiness, and, if necessary, medical clearance will be obtained. The Physical Activity Readiness Questionnaire will be used for this purpose [31]. Exclusion criteria are as follows: (1) medical contraindications for participation in programs with increased exercise, as advised by the primary care or ID specialist physician; (2) high levels of PA; and (3) inability to provide written informed consent or consent cannot be obtained from a legal representative.

### Ethics Approval

All participants and their caregivers will receive information about the purpose and procedures for the study. Informed consent will be obtained from the individuals with ID, as far as possible, if the person has decision-making capability to provide consent. In addition, or in case the person with ID cannot provide consent, a caregiver will provide informed consent on behalf of the person with ID. The definite trial and the pilot study have been approved by the Regional Committees for Medical and Health Research Ethics in Norway (2016/1770) and the data protection officer at the University Hospital of North Norway.

### Intervention

The final app is named Active Leisure (Aktiv Fritid) and consists of an advanced activity planner based on the platform developed by the nonprofit organization Smart Cognition AS (Smart Cognition AS). The app offers various interface options (symbols only, easy-to-read text, plain text, and read aloud). See Multimedia Appendix 1 for interface options for the Active Leisure app. The activity planner will mostly be used by an individual with ID and a support person (caregiver or health care provider). Participants will have different levels of functioning and will require different proximity of support persons, which will be considered when delivering the intervention. After completing an activity, a simple reward is available (eg, a smiling face or to share a picture with other users of the app). All activities that go into the activity planner are added through a web application. For this project, the principal author (HM) will be responsible for adding personalized activities into the activity planner for each participant. The use of tailored communication [32] through personalization (the use of the individual’s first name in the activity planner), adaptation (individually chosen activities, adjusted communication, including symbols, easy-to-read text, or plain text), preparation and planning, and feedback (rewarding and positive feedback after activities have been performed) are expected to increase motivation and thereby lead to higher levels of PA.

An individual mHealth exercise app has also been developed as a potential alternative that can be added to the Active Leisure planner; this app is called Sorterius (see Multimedia Appendix 2) [33] and is an augmented reality game, inspired by the popular game Pokémon Go. In this app, individuals can use the camera on their phone to look for virtual waste on the ground. Virtual waste will appear as they walk and can be sorted into correct waste bins, depending on the level of difficulty chosen (easy=1 waste bin, medium=2 waste bins, difficult=4 waste bins). When a set number of items has been collected, the individual will receive a virtual reward (stars and positive feedback). It is possible to add goals for steps per day and a weekly goal, which can be tailored to each individual’s interest.

### Data Collection

#### Procedure

Three research nurses from the clinical trial unit at the University Hospital of North Norway will support study procedures. Participants will be screened for readiness via telephone. The participants’ closest relative or guardian or a support person approved by the participants will be contacted for a baseline assessment via telephone. Questionnaires will be sent over email using the electronic system Research Electronic Data Capture (REDCap), a web-based system that is compliant with relevant regulations and security requirements. The study coordinator will evaluate the data of all participants for completeness. In cases of missing data, respondents will be contacted. Two activity trackers (Fitbit and Axivity), to be worn for 7 consecutive days, will be handed to participants after the baseline assessment. According to the instructions, Fitbit will be used on the dominant hand and Axivity on the nondominant hand. Participants who only accept to use one of the activity trackers will use the Fitbit device, as PA output from this device will be used to assess study outcomes in a later definite trial. After baseline assessments, participants and caregivers or staff will be invited to a goal-setting meeting where the Goal Attainment Scale will be used, and they will be introduced to the mHealth application Active Leisure and a motivating augmented reality application for sorting waste, called “Sorterius” [33]. Caregivers or staff will receive a telephone call from the study nurse at 4-week follow-up and asked to complete the questionnaires via email. The study nurse will also as ask caregivers or staff about the use of the activity trackers and ask for general comments regarding study procedures. These data will be added in the electronic system REDCap. Subsequently, they will receive the activity trackers again. The same procedure will be followed at the 12-week follow-up. Technical support will be available during the study period. After the end of the pilot trial, all participants and caregivers or support persons or staff will be asked to take part in a semistructured interview to share their experiences from the study.

#### Demographics, Level of ID, and Baseline Functioning

Background data of the participants, such as age, gender, educational level, marital status, living condition, employment status, educational status, job-related or day-center activities, leisure time activities, smoking habits, level of ID (ie, mild, moderate, severe, or profound), genetic diagnosis, medical history or readiness for the PA intervention, and use of medication will be collected at baseline. Ratings of the 5-level Gross Motor Function Classification System and the Communication Function Classification System will also be collected during baseline assessments [34-36].

#### Qualitative Interview

The recruited participants and their caregivers or a staff member in the pilot study will be asked to participate in a 1-hour qualitative interview after the 12-week follow-up assessment. A semistructured interview will take place at the participant’s home or other locations convenient for the participant, caregiver, or staff member [37]. Given the cognitive and speech limitations of many people with ID, semistructured interviews will be performed with the person with ID along with a caregiver or staff member, or only performed with the caregiver or staff member. Therefore, at least for the proxy interviews comprising participants unable to answer the questions, the interviews need to be arranged to facilitate an interpretation that reflects the participants opinions or attitudes. An interview guide has been developed and will be used in the interviews [26]. The interview guide will be categorized into 2 sections. Section 1 will focus on feasibility and acceptability of procedures, how the mHealth support will be used, and participant and caregiver or staff experiences of participation in all aspects of the study. Section 2 will focus on motivation for using technology to enhance PA levels, how the environment around the person with ID can use technology for PA, and practical barriers for using technology in an everyday setting. All interviews will be audiotaped, transcribed verbatim, and anonymized.

#### Aspects of Feasibility

To assess feasibility, recruitment, adherence to the intervention, retention, and completeness of data will be evaluated. Recruitment will be evaluated from the number of invited participants, eligible, and recruited or not recruited participants. We expect to include 1-2 eligible participants with ID per week. The expected recruitment rate is 20%; that is, 20% of eligible individuals are expected to agree to be enrolled. Adherence to the intervention will be evaluated through information about the actual use of the applications, which will be obtained from the qualitative interviews. Retention is defined as the number of participants who complete all 3 assessments and the qualitative interview. We expect 80% of the participants to complete the assessments and the interviews. Completeness of quantitative data (missing) will be recorded, and less than 10% data are expected to be missing. Adverse events will be reported to the researchers or the study nurses.

#### Outcome Measures in the Definite RCT

To assess the planned primary outcome in the definite trial PA level (accelerometer measured steps per day) [26], the participants will use one Fitbit device (Versa). The watch will show a neutral screen during baseline and follow-up assessments. Participants who consent will, in addition, use one device manufactured for scientific purposes (Axivity AX3). Axivity will be used to assess the validity of the Fitbit Versa. This will objectively assess PA and sedentary time [38]. The PA level will be measured for 7 days at each assessment, with a minimum of 3 consecutive days of measurement [8]. Only days with at least 10 hours of wear time will be considered valid [39]. Many of the commercial fitness trackers have been validated for use in the research, including devices from Fitbit [40-42]. The primary outcome in the definite trial will be objectively measured PA assessed by increase in steps per day from the Fitbit device for each participant.

Several secondary outcome measures are explored: minutes of moderate activity, the International Physical Activity Questionnaire Short, BMI, and goal attainment [43-46]. Proxy respondent measures include measures of aberrant behavior (the Aberrant Behaviour Checklist-Community), social support for PA and self-efficacy in a PA setting, and health status (the EQ-5D scale) [47-49]. To control for adverse effects, an adapted quality-of-life scale will be assessed [50]. These measures will be used as evaluation of the sensitivity of the data to detect change and as part of testing the procedures for a later RCT. All these measures have previously been used in research with individuals with ID, and more information about each of these measures can be found in the protocol article for the planned RCT [27].

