### Data Analyses

#### Quantitative Data

Appropriate quantitative statistical analyses will be performed using SPSS (version 28; IBM Corp) in accordance with the type and distribution of data. The descriptive statistics are presented as median (IQR) values, means with SDs or 95% CIs, and frequencies of categorical data. The distributional properties of variables will be examined. Hypothesis testing will not be performed. In concordance with the Consolidated Standards of Reporting Trials (CONSORT) 2010 extension, estimates of effects using participant outcome measures (differences from baseline to postintervention) will be explored and reported as estimates with 95% CIs without *P* values [51,52]. We shall also perform mixed analyses; quantitative data can be supplemented from information in the qualitative material. For instance, if there is a change in the activity data, interviews can shed light on whether changes are related to the use of technology or whether other mechanisms are involved.

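### Minor: the 3-consecutive-day tracker rule can reject weeks with more valid days than weeks it accepts; any 3 valid days would serve mean steps per day as well

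*Protocol article*

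**What the plan says.** The rule is in the protocol article under Outcome Measures in the Definite RCT: "The PA level will be measured for 7 days at each assessment, with a minimum of 3 consecutive days of measurement". Shortly afterwards the same section defines a valid day: "Only days with at least 10 hours of wear time will be considered valid". Under Procedure, the trackers are "to be worn for 7 consecutive days".

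The measure built on these days is the planned RCT's primary outcome, "assessed by increase in steps per day from the Fitbit device for each participant". The pilot uses it too: under Quantitative Data, "estimates of effects using participant outcome measures (differences from baseline to postintervention) will be explored", with 95% confidence intervals and no P values. Under Aspects of Feasibility the article adds: "Completeness of quantitative data (missing) will be recorded, and less than 10% data are expected to be missing". It does not say whether that expectation refers to tracker days, tracker weeks or questionnaire items.

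**The concern.** Taken together, the two sentences ask for three valid days in a row. The outcome is an average over days, and an average does not depend on whether its days are adjacent. The rule therefore ranks weeks by something irrelevant to the estimate: a week with five valid days can fail where a week with three passes.

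At stake is the number of participants who contribute a steps-per-day value at each assessment, and hence a change from baseline, in a study of 10. Completeness is also a feasibility result here, so an avoidable loss through the definition could make the trackers look less workable for the RCT than they are.

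**Working it through.** **Inputs.** From the article: a 7-day wear period, a minimum run of 3 days, and the 10-hour valid-day rule. Assumed, because the article gives no figure: the daily probability q that a day is valid, and independence between days. The article has no figure of its own on this point to reproduce.

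**Step 1: which weeks fail.** A week has 2^7 = 128 valid/invalid patterns. Write V for a valid day and x for an invalid one.

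| Valid days | Patterns | Fail 3 consecutive | Pass |
|---|---|---|---|
| 3 | 35 | 30 | 5 |
| 4 | 35 | 19 | 16 |
| 5 | 21 | 3 | 18 |
| 6 | 7 | 0 | 7 |
| 7 | 1 | 0 | 1 |

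The three failing five-day patterns are VVxVVxV, VVxVxVV and VxVVxVV. With six valid days a run of three always exists. In all, 30 + 19 + 3 = 52 of the 99 patterns with at least three valid days fail.

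**Step 2: share of weeks kept.**

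- 3 consecutive: 5q³(1−q)⁴ + 16q⁴(1−q)³ + 18q⁵(1−q)² + 7q⁶(1−q) + q⁷
- Any 3 valid: the binomial probability of 3 or more valid days out of 7

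At q = 0.7 the first is 0.014 + 0.104 + 0.272 + 0.247 + 0.082 = 0.719, and the second is 0.971.

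| q (assumed) | 3 consecutive | Any 3 valid | Lost through adjacency alone |
|---|---|---|---|
| 0.6 | 54.3% | 90.4% | 36.1% |
| 0.7 | 71.9% | 97.1% | 25.2% |
| 0.8 | 86.9% | 99.5% | 12.6% |
| 0.9 | 96.7% | over 99.9% | 3.2% |

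Per assessment of 10 participants, the last column amounts to about 3.6, 2.5, 1.3 and 0.3 weeks.

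A change score needs two usable weeks. Squaring, with the two weeks also treated as independent, gives 0.719² = 0.52 against 0.971² = 0.94 at q = 0.7. At q = 0.9 it gives 0.936 against 0.9996.

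**Step 3: the other end of the range.** Suppose a participant wears the tracker for the first m days and then stops. The valid days form one block, so a run of three exists exactly when m is 3 or more. The two rules keep the same weeks, and the loss is zero.

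**Step 4: day type.** Of the seven possible three-day runs, three contain no weekend day, two contain one and two contain two. If the weekday-weekend gap is G steps per day, a Monday-Wednesday baseline against a Friday-Sunday follow-up shows an apparent change of (2/3)G. With an assumed G of 1,000 to 2,000 that is 667 to 1,333 steps per day.

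The share of retained pairs with this 0 versus 2/3 mix, in either order, at q = 0.7:

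- 3 consecutive, least favourable start day (Friday): no weekend day, 0.09 × (2 × 0.7³ × 0.3 + 0.7⁴) = 0.0401; two weekend days in three, 2 × 0.7³ × 0.3⁴ = 0.00556. Share = 2 × 0.0401 × 0.00556 / 0.517 = 0.09%.
- Any 3 valid: 0.09 × 0.837 = 0.0753 and 5 × 0.7³ × 0.3⁴ = 0.0139. Share = 2 × 0.0753 × 0.0139 / 0.943 = 0.22%.

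The extreme mix is very rare under either rule, and rarer under the existing one.

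**The case against.** The strongest reply is that the loss depends on how wear fails. A reader might infer that the article anticipates intermittent wear. It does not: Potential Limitations and Implications describes participants not accepting two trackers and stopping their use, which leaves contiguous days and no loss. The general remarks on missing data under Expected Findings do not describe a day-by-day pattern. Independent daily validity is an assumption of this check, so the 0.94 against 0.52 contrast is one point in a range and not a forecast. This part of the reply stands.

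It is also fair that the five-valid-day failure is a worst case, that the minimum comes with a citation, and that discarding weeks below it is implied and not written. None of this gives adjacency a role in a mean of steps per day.

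A stronger reading is that the rule lets weekday-only and weekend-heavy weeks pass as change in activity. The article does not support this as a main finding. Participants are asked for seven consecutive days, so a complete week always has five weekdays and two weekend days. The extreme mix is very rare (step 4), and dropping adjacency makes it slightly more common. Day-type weighting is a derivation detail that an article may leave to a fuller document. Milder imbalances remain possible; they add noise, and they bias the change only if the mix shifts systematically between assessments.

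**Conclusion.** The point holds as a minor one. As stated, the rule can reject weeks with three or four scattered valid days, exceptionally five, while keeping a bare three-day run, with no gain for the outcome. The avoidable loss ranges from nil, if non-wear is a single early stop, through 3% of weeks at 90% independent daily validity, to 25% at 70% and 36% at 60%.

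This rests on two readings, that the three consecutive days must each be valid and that weeks below the minimum are not used, and on assumed validity rates. A reader might set the 13% of weeks failing at 80% validity (1 − 0.869) against the article's expectation of under 10% missing data and conclude that the rule defeats the target. The unit of that target is undefined and the 80% is assumed, so the article does not support that conclusion.

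Severity is limited because the pilot has 10 participants, one arm and no hypothesis tests. The reason to act is that the same rule is attached to the RCT's primary outcome.

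**What to change.** Define a usable assessment as any three or more days with at least 10 hours of wear, not necessarily consecutive. Apply the same definition to Fitbit and Axivity. Report the 3-consecutive-day version as a sensitivity analysis, and state how many weeks each definition keeps; that count is itself useful feasibility information for the RCT.

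As a secondary refinement only, compute steps per day as 5/7 of the weekday mean plus 2/7 of the weekend mean where both exist, and report the day-type mix of weeks that lack one. The weighting cannot correct a week with no weekend day, which is why the mix should be shown.

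The cost is one changed sentence, a simple derivation and slightly less comparability with the cited study. The article reports data collection as complete, so for the pilot this is a change in deriving the outcome from the daily records. It should be declared as such, with both versions shown.
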